## Abstract

**Background:**

Exercise rehabilitation is essential for improving the prognosis of patients after percutaneous coronary intervention. However, patients’ adherence to exercise rehabilitation is generally low. Existing health education interventions focus on the supply of message content, but generally ignore the impact of message expression on patients’ cognition and behavior, which limits the promotional effect of health education to a certain extent. The theory of message framing effects states that even a message that is essentially the same can have a differential impact on an individual’s behavioral decision-making through different ways of presenting it.

**Objective:**

This study aims to develop an educational program for exercise rehabilitation of post-PCI patients based on the effect of message framing, and to investigate the effects on exercise rehabilitation by integrating the gain-versus loss-framing and narrative versus non-narrative framing.

**Methods:**

In this study, we will first construct an exercise rehabilitation education program for post-PCI patients based on the message framing effect through qualitative interviews, evidence integration and Delphi expert consultation. A video-based presentation format will be developed simultaneously to deliver the intervention content. Subsequently, a 2 (gain vs. loss framing) × 2 (narrative vs. non-narrative framing) factorial randomized controlled design will be employed. Participants will be randomly assigned to four intervention groups to receive a three-week rehabilitation education intervention based on different message framing conditions. The primary outcome indicator is exercise adherence, and secondary outcomes include exercise intention, exercise fear, exercise self-efficacy and quality of life. Data will be collected at three time points: baseline, 1-month and 3-month post-intervention. Statistical analyses will be conducted using SPSS 25.0 and R 4.3.2 software, with linear mixed-effects models employed to assess the impact of different message framing conditions on primary and secondary outcomes across multiple time points.

**Discussion:**

This study will provide an innovative research method and a practical basis for exploring the optimal application of message framing effect in cardiac rehabilitation.

**Clinical trial registration:**

https://www.chictr.org.cn/index.html, Identifier ChiCTR2400087233.

Health message serves as a vital bridge between medical research findings and public health knowledge, attitudes, and behaviors (14). The accuracy, efficacy, and timeliness of its dissemination shape individuals’ understanding of health issues and, consequently, drive changes in health behaviors. Patients with cardiovascular disease often lack timely and effective message support at the time of hospital discharge, which greatly affects their motivation to participate in exercise rehabilitation (15). However, existing intervention studies on postoperative exercise adherence in PCI are mostly centered on health education, with messages delivered through educational brochures, bedside guidance, and short video pushes (16). Most of these studies are based on the perspective of healthcare supply, ignoring individual differences in patients’ cognitive level, emotional state, and message processing preferences, resulting in limited acceptance of the message, and patients’ low acceptance of the message on exercise rehabilitation, which eventually affects their willingness to participate in exercise and adherence to exercise (17).

The framing effect refers to the fact that different ways of describing a message based on the same problem result in generating different decision-making behaviors (18). Message framing examines how the presentation of a message influences the individual-message interaction, providing a new approach to studying how health communication drives behavior change (19). The message framing effect has been employed across various health domains, including disease detection (20, 21), vaccination (22, 23), smoking cessation (24), and physical exercise (25, 26). Prevalent message framing in health behavior research includes gain-loss framing, narrative framing, and temporal framing (27). The gain-loss framing is the most widely used type of goal framing, as it presents different forms of a message that is substantively the same by emphasizing the benefits to the individual of accepting a particular health behavior and the losses resulting from rejecting that behavior. However, the effectiveness of gain-loss framing in promoting improvement in individual health behaviors is controversial and has been less explored, especially in chronic disease conditions such as coronary heart disease, where there are fewer relevant studies with mixed results (28–30). In recent years, narrative framing has received increasing attention for its ability to enhance behavioral decision-making through the use of vivid, concrete stories that evoke emotional resonance and increase the acceptability, persuasiveness and memorability of the message (31). Research has shown that combining the gain-loss and the narrative framing can be more effective in enhancing the management of self-healthy behaviors (32, 33). Time framing influences individuals’ risk perceptions and behavioral intentions by altering their perceptions of time duration (34). Due to the repetitive and short-term nature of post-operative exercise rehabilitation after PCI, as well as increased patient risk awareness, time framing will not be included in the study. Instead, the study will focus on the integration of narrative and gain–loss framing.

## Objective

The study objectives are:

To investigate the characteristics of the message needs of exercise rehabilitation for post-PCI patients, and further construct an exercise rehabilitation education program for post-PCI patients based on the message framing effect through the summary of evidence and the Delphi method of expert correspondence.To conduct a preliminary application of the exercise rehabilitation education program, exploring the effectiveness of differently framed exercise rehabilitation education.

## Methods

### Study design

This is a two-phase study:

*Phase 1*: We will develop an exercise rehabilitation education program for post-PCI patients based on the message framing effect through qualitative needs assessment, evidence synthesis, and expert consensus.*Phase 2*: We will conduct a prospective, parallel-controlled, single-blind randomized controlled trial using a 2 (gain vs. loss framing) × 2 (narrative vs. non-narrative framing) factorial design to implement the exercise rehabilitation education program, comprising four groups: Group A (gain-narrative framed message), Group B (loss-narrative framed message), Group C (gain-framed non-narrative message), and Group D (loss-framed non-narrative message). This phase includes a 3-week intervention period and a 3-month follow-up period. The study design is shown in Figure 1.

**Figure 1 fig1:**
[figure not shown]
Study design and participant flow.

## Phase 1: development of an exercise rehabilitation education program for post-PCI patients based on message framing effect

### Qualitative study

A qualitative descriptive study will be conducted to gain insight into patients’ experiences, perceived barriers, expectations, and message needs, such as content preferences, access, and the form in which the message will be presented in relation to exercise rehabilitation after PCI. We will use a purposive maximum variance sampling strategy to recruit patients who have undergone PCI from the Department of Cardiology of a tertiary care hospital in Hangzhou, China. Participants must be adults (≥18 years old) who are clinically stable and assessed to be at low exercise risk after PCI, and all patients should sign an informed consent form. Patients with physical activity impairments, severe comorbidities, cognitive/communication impairments, or participation in other studies will be excluded. Qualitative data will be collected through semi-structured interviews using a protocol developed from a literature review and preliminary team discussions. Key topics include patient perceptions of exercise after PCI, past experiences, concerns, instruction received, and preferences for content and delivery. Interviews, lasting 30–45 min, will be audio-recorded, transcribed verbatim within 24 h, and supplemented by field notes. The transcribed texts will undergo independent coding by two researchers using thematic analysis with NVivo 12.0. Through an iterative process, codes will be compared, discussed, and refined to identify and agree upon key themes.

### Literature review and summary of evidence

A systematic evidence review will be conducted to ensure the scientific validity of the education program. A comprehensive literature search will be conducted in major electronic databases (including PubMed, Embase, Cochrane Library, CNKI and Wanfang) and guideline repositories (e.g., GIN, NICE, AHA and ESC). The inclusion criteria for the literature are as follows: (1) study population comprising post-percutaneous coronary intervention patients; (2) interventions involving cardiac exercise rehabilitation; (3) publication types limited to clinical guidelines, evidence summaries, recommended practices, expert consensuses, or systematic reviews. The exclusion criteria are as follows: (1) literature unrelated to the topic or duplicates; (2) conference abstracts, letters, incomplete data, or literature for which the full text is not available; (3) literature not published in Chinese or English. During the search process, a combination of subject terms and free terms will be used to search for core concepts.

### Delphi expert consultation

A Delphi expert correspondence method will be organized to refine and modify an initially developed exercise rehabilitation education program for patients after PCI. Experts from relevant fields such as cardiology, rehabilitation medicine, nursing, nursing education, and chronic disease management will be purposively selected. The criteria for selection of experts include: (1) undergraduate degree or higher; (2) intermediate or higher title; (3) more than 5 years of relevant work experience; (4) voluntary participation. The target number of experts is 15–50. The Delphi process will consist of two rounds of online consultations conducted via email or WeChat. In each round, experts will receive a questionnaire covering the following areas: their demographic and professional background, self-assessment of their judgment basis and familiarity with the content, and the draft education plan. They will be asked to rate the importance of each plan item on a five-point Likert scale and to provide open-ended revision comments. Data analysis, including assessments of expert response rates, authority coefficients, coordination of opinions, and concentration of feedback, will be performed using Excel 2019 and SPSS 25.0. We will organize discussions based on the feedback from experts to complete the revision and improvement. The screening criteria for items will be: a mean importance score >3.5 and a coefficient of variation <0.25. For those entries that do not meet the above criteria, the group will conduct a comprehensive discussion to collectively decide whether to retain, revise, or delete them.

### Pre-experimental

A purposive sampling method will be adopted to invite post-PCI patients hospitalized in the Department of Cardiology of a tertiary hospital in Zhejiang Province to experience the educational program. After obtaining the patients’ consent, they will be invited to watch the exercise rehabilitation education video and encouraged to ask any questions and give feedback, and the education program will be further modified and optimized according to the patients’ opinions.

### Final draft

Unlike traditional educational formats, this study will innovatively combine the theory of message framing effect, centring on the knowledge of exercise rehabilitation of aerobic exercise, resistance training and flexibility training, and present each exercise from the perspective of the benefits of exercise and the risks associated with inactivity. Real-life case studies will also be incorporated, resulting in the final draft of the rehabilitation education program for post-PCI patients. Through the combination of gain-loss framing and narrative framing, four groups of differentiated educational materials will be developed. The gain framing will emphasize the positive outcomes and benefits patients can achieve through exercise rehabilitation, such as improved cardiac function, reduced risk of cardiovascular events, enhanced physical strength, and improved quality of life. The loss framing will highlight the negative consequences and potential losses patients may face if they do not follow exercise rehabilitation recommendations. Additionally, by using specific patient stories of exercise rehabilitation and employing emotional narratives, the narrative framing will enhance patients’ emotional resonance and understanding, thereby better promoting the implementation of exercise rehabilitation education. Considering that most patients with coronary heart disease are older adults and that many experience age-related visual impairment, which makes reading and understanding text difficult, they tend to prefer receiving exercise rehabilitation education messages in video format for easier comprehension and learning. Based on the findings of the literature review and qualitative interviews, animated video presentations are therefore incorporated in addition to the text-based exercise rehabilitation education program. The videos will be designed to present the textual content of the educational messages in bold characters, with appropriate pictures, animations, voice-overs and background music to enhance the readability and interest of the videos, and the length of each video will be controlled to be within the range of 3–6 min.

## Phase 2: application of the exercise rehabilitation education program

### Study setting

This randomized controlled trial will use consecutive sampling to recruit participants from the cardiovascular department of a tertiary-level general hospital in Zhejiang Province.

### Patients

Patient recruitment will be managed by experienced clinical nurses. Before recruitment, these nurses will receive comprehensive training from the research team on the study’s objectives, methods, and procedures. Leveraging their familiarity with the patients’ specific conditions, the nurses will ensure a professional and efficient recruitment process. Following recruitment, a member of the research team will provide a standardized explanation of the study’s purpose and significance to all participants. Special emphasis will be placed on the confidentiality agreement, explicitly instructing patients not to discuss the intervention details with other participants. This process is designed to address patient concerns, enhance intervention adherence, and ensure the integrity of the trial. The researcher will assure participants that their personal information will remain strictly confidential and will be used solely for scientific research and publication. It will be clearly stated that participants can withdraw from the study at any time without penalty or consequence. Written informed consent will be obtained from all eligible participants before any data collection. Table 1 displays the patient inclusion and exclusion criteria, as well as shedding details.

**Table 1 tab1:** Patient inclusion, exclusion and shedding criteria.

Criteria	Content
Inclusion criteria	Patients who have undergone PCI; Patients aged greater than or equal to 18 years; Stable condition post-surgery, with no severe cardiovascular complications; Patients assessed as low-risk for exercise rehabilitation post-PCI according to the *Expert Consensus on Exercise Rehabilitation After Percutaneous Coronary Intervention;* Patients can manipulate a smartphone with WeChat independently, or have a co-residing primary caregiver (who fulfils these technical criteria) to assist them;
Exclusion criteria	Individuals with physical mobility impairments; Malignant tumors or other serious complications; Pregnant or breastfeeding individuals; Mental illness, cognitive impairments, or language communication barriers; Individuals currently participating in other studies;
Shedding criteria	Voluntary withdrawal from the study; Loss to follow-up; Participants failing to complete the video-based intervention as required; The occurrence of any serious adverse event or a significant deterioration in health status during the trial period;

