1 week after discharge	Aerobic exercise guidance	Gain frame	Loss frame	Gain frame	Loss frame	WeChat
2 Weeks after discharge	Resistance exercise guidance	Gain frame	Loss frame	Gain frame	Loss frame	WeChat
3 Weeks after discharge	Flexibility exercise guidance	Gain-narrative frame	Loss-narrative frame	Gain frame	Loss frame	WeChat

During the intervention period, patients in all four groups can continue to receive their regular medical treatment and rehabilitation management (e.g., medication, dietary adjustments, psychological support, etc.), which are assessed to be compatible with the intervention content of this trial and are not expected to affect the effectiveness of the intervention. If patients need to receive other treatments (e.g., surgery, emergency treatment, etc.) or adjust their routine treatment due to health problems during the trial period, the research team will assess whether these treatments affect the efficacy and credibility of the findings of the trial and decide whether participants can continue to participate in the study. In addition, any additional treatments or medications other than routine treatment will be reported to the research team in advance and will be evaluated by the research team as appropriate to ensure that they do not adversely affect the trial intervention.

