### Data statistics and analysis

Statistical analysis of the data will be performed using SPSS 25.0 and R 4.3.2 software. All statistical analyzes will be conducted using two-sided tests, with a significance level set at *p* < 0.05. Continuous variables will be described using mean ± standard deviation, while categorical variables will be expressed as frequency (n) and percentage (%). For intergroup comparisons of baseline data: continuous variables that follow a normal distribution will be compared using one-way analysis of variance (ANOVA); those that do not follow a normal distribution will be compared using the Kruskal–Wallis nonparametric test. Categorical variables will be compared using the chi-square test or Fisher’s exact test, as appropriate.

To comprehensively analyze changes in outcome indicators across different groups and time points following the intervention, data will be analyzed using a linear mixed-effects model (LMM). The gain-loss framing, narrative framing, and time will be included as fixed effects, while individual study participants will be included as random effects to account for individual variability. The LMM model will be constructed to assess the main effects of the gain-loss framing, narrative framing, and time, as well as their interaction effects. If the interaction effects are significant, further analysis of the simple effects of the message framing and time will be conducted to explore the impact of the intervention on outcome indicators at different time points. If interaction effects are not significant but main effects are, Tukey’s HSD *post hoc* comparison analysis will be further conducted to explore the independent effects of different message framing and time points on outcome indicators. The LMM model uses maximum likelihood estimation and is able to fit the model efficiently using all available data containing missing values, and is therefore robust to missing data.

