As this is a single-center study conducted at a tertiary-level hospital in Zhejiang Province, the sample size is relatively small. This may result in certain regional limitations and insufficient sample representativeness, potentially limiting the generalisability of the study findings to patients in other regions or different types of hospitals. To enhance the external validity of the study results, future research could recruit more patients from multi-center, cross-regional studies, encompassing different types of healthcare institutions and social backgrounds, thereby providing a more comprehensive and accurate assessment of the impact of the message framing on post-PCI patient exercise rehabilitation.

During the implementation phase of the intervention, although we can remind patients to watch the video via WeChat or telephone, we still cannot guarantee that each patient has carefully watched all the video content, which may be a limitation.

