## Ethics and dissemination

The study was approved by the Ethics Committee of the Second Affiliated Hospital, Zhejiang University School of Medicine, Hangzhou, China (Ethics approval: No. 2024-0576). The full trial protocol and statistical analysis plan are available in the Chinese Clinical Trial Registry. Before the investigation, the researchers will inform all participants about the purpose and procedures of the study, ensuring that their personal information will remain strictly confidential in accordance with data protection principles. The collected data can be used solely for scientific research and publication. Written informed consent will be obtained from all participants prior to data collection. Participants will be informed that their participation is entirely voluntary and that they may withdraw from the study at any time without penalty. Participants who self-report or are identified during follow-up as having sustained injuries or a deterioration in health directly related to the study procedures will have their participation in the relevant portion of the study terminated early, following physician evaluation. Affected individuals will receive appropriate medical treatment and corresponding compensation.

Any significant changes to the protocol will first be discussed within the research team, reviewed by the principal investigator, and subsequently submitted to the institutional ethics committee for approval. All relevant parties, including investigators and the trial registry, will be informed of the approved amendments.

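### Counting patients who do not finish the videos as having left the trial can tie missing outcomes to engagement, and the claim that the mixed model is robust to missing data does not cover this

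*Protocol article*

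**What the plan says.** The protocol article deals with patients leaving the trial in several places.

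- **Patients, Table 1.** The shedding criteria are voluntary withdrawal, loss to follow-up, "Participants failing to complete the video-based intervention as required", and "The occurrence of any serious adverse event or a significant deterioration in health status during the trial period".
- **Interventions.** For patients who need other treatment or a change in routine treatment, "the research team will assess whether these treatments affect the efficacy and credibility of the findings of the trial" and then "decide whether participants can continue to participate in the study".
- **Ethics and dissemination.** Patients with injury or deterioration directly related to study procedures "will have their participation in the relevant portion of the study terminated early", after a physician's evaluation.
- **Data statistics and analysis.** The linear mixed model is fitted by maximum likelihood, "using all available data containing missing values, and is therefore robust to missing data".
- **Design justification and constraints.** There is no conventional-education arm, and a pre-post comparison is offered in response. On viewing, "we still cannot guarantee that each patient has carefully watched all the video content".

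The primary outcome is an exercise adherence scale. It is measured at baseline and at 1 and 3 months after the intervention, by online form with a telephone call as back-up (Data collection and outcomes).

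**The concern.** Not finishing the videos happens after randomisation, and it is a response to the randomised material. From the week-1 video onward that material differs between gain and loss framing, so the frame may influence who finishes. The primary scale covers exercise adherence, exercise monitoring and seeking advice, so engagement with the videos is plausibly related to it.

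Table 1 puts a patient who is reachable and consenting but has stopped watching in the same class as one who has withdrawn. If that patient is then not sent the 1- and 3-month questionnaires, only the baseline value remains. Two things could follow:

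- Follow-up means would describe the more engaged patients, and the pre-post change would look larger than it is.
- If one frame sheds more patients than the other, the contrast would favour the frame that lost more of its reluctant patients.

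The treatment-related rule in Interventions could have a similar effect through health. It turns on a judgement about the trial's efficacy and credibility, and the article describes blinding only for participants.

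**Working it through.** **1. The plan's own figure.** Sample size states a total of 100 with 20% dropout. 80 / (1 − 0.20) = 100, so the total fits 80 evaluable patients, 20 per group. The base of 80 cannot be rebuilt from the article, which gives no effect size, SD or power; that is not counted against it. For scale, a framing main effect compares 40 with 40 evaluable patients. The difference detectable with 80% power at two-sided 0.05 is (1.960 + 0.842) × √(2/40) = 0.63 SD.

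**2. Assumptions.** The documents give neither a shedding rate by arm nor an engagement-adherence correlation. The following are assumed:

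- Engagement and adherence are bivariate normal with correlation r of 0.2 to 0.5.
- The least engaged fraction p is shed and contributes no follow-up outcome.
- There is no true framing effect.
- 50 patients are randomised per factor level.
- There is no adjustment for baseline.

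**3. Shift in the retained mean.** E[Y | retained] = r × m(p), where m(p) = φ(z_p)/(1 − p).

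| p shed | m(p) |
|---|---|
| 0.10 | 0.1755/0.90 = 0.195 |
| 0.15 | 0.2332/0.85 = 0.274 |
| 0.20 | 0.2800/0.80 = 0.350 |
| 0.25 | 0.3178/0.75 = 0.424 |
| 0.30 | 0.3477/0.70 = 0.497 |

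At 20% shedding the shift is 0.2 × 0.350 = 0.07 SD, 0.3 × 0.350 = 0.105 SD, or 0.5 × 0.350 = 0.175 SD. It is present even when all arms shed equally.

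**4. Bias between frames.** Bias = r × [m(p₂) − m(p₁)]. The standard error uses the retained numbers and the outcome variance after truncation. Type I error is the chance of exceeding ±1.96 given that bias.

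| Shed | r | Bias (SD) | Type I error |
|---|---|---|---|
| 20% v 20% | any | 0 | 0.050 |
| 15% v 25% | 0.2 | 0.030 | 0.052 |
| 15% v 25% | 0.3 | 0.045 | 0.055 |
| 15% v 25% | 0.5 | 0.075 | 0.064 |
| 10% v 30% | 0.2 | 0.060 | 0.058 |
| 10% v 30% | 0.3 | 0.091 | 0.069 |
| 10% v 30% | 0.5 | 0.151 | 0.109 |

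With unit variance, the 10% v 30% case has SE = √(1/45 + 1/35) = 0.225. Type I error is then 0.069 at r = 0.3 and 0.103 at r = 0.5. A simulation of two million draws at r = 0.5 gave 0.176 for the 20% shift and 0.151 for the 10% v 30% bias, in agreement with the formulas.

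**5. What the mixed model covers.** Likelihood estimation on all available data is valid if missingness depends only on what is observed and modelled. The stated fixed effects are the two framing factors and time, and engagement is not among them. Baseline adherence is in the data and can absorb part of the selection, to the extent that it reflects engagement. Step 4 is a completers-only contrast, so it does not evaluate the planned model.

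**6. The two safety statements side by side.** Table 1 covers any serious adverse event or significant deterioration, and the consequence is shedding. Ethics and dissemination covers harm directly related to study procedures, and the consequence is ending the relevant portion. The narrower case lies within the broader one, but the stated consequences differ.

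**The case against.** The strongest objection is that the article never says shed patients leave the analysis or stop receiving questionnaires. A reader might infer from Table 1 that they are no longer counted. The documents do not support that: the model uses all available data, and analysis populations may be set out in the statistical analysis plan, which the article says is in the registry. This stands, so the point has to be conditional. It does not remove the point, because an analysis plan cannot recover questionnaires that were never collected.

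Other parts of the objection also stand:

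- A reader might treat the team's judgement on efficacy as another shedding criterion that selects on engagement. It is in Interventions, not Table 1, and it concerns patients who need other treatment. Such exits, and those after serious adverse events, select on health.
- A reader might take the admission about careful watching to mean that viewing cannot be checked. It concerns attentiveness. Interventions describes a guided first viewing and two content questions after each weekly video.
- The 10% v 30% split is assumed, and its average uses the whole 20% dropout allowance. It is hard to justify for the narrative factor: in Table 2 the narrative and non-narrative groups carry the same frame labels until the week-3 video.
- The planned model uses the baseline measure, which the illustration leaves out.

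**Conclusion.** The point holds in conditional form. Table 1 treats non-completion of the randomised videos as leaving the study. If those patients are not followed, missing outcomes will depend on engagement, and the article's assurance about missing data does not extend to that. This can bias the results; it does not show that they will be biased.

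The size depends on assumptions that the documents cannot confirm. At 20% shedding, retained means rise by 0.10 to 0.18 SD for correlations of 0.3 to 0.5, which matters for the pre-post reading. Between frames there is no bias under equal shedding in this model. At 15% v 25% it is 0.03 to 0.075 SD (correlation 0.2 to 0.5), with type I error of about 5% to 6%. At 10% v 30% it is 0.09 to 0.15 SD (correlation 0.3 to 0.5), with type I error of about 7% to 10%. Against a detectable main effect of about 0.63 SD, the between-frame bias is small to moderate. Baseline adherence in the planned model may reduce it by an unknown amount.

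The safety statements in Table 1 and in Ethics and dissemination need reconciling as to reach. No view is taken on the clinical rule.

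**What to change.** - **Table 1.** Remove video non-completion from the shedding criteria and record it as intervention compliance. Separate stopping the intervention from leaving the study.
- **Follow-up.** Collect the planned 1- and 3-month questionnaires from every randomised patient who has not withdrawn consent. This includes those who stop viewing, those who receive other treatment under the Interventions rule, and those whose participation in the intervention ends for safety.
- **Analysis.** Analyse all randomised patients in their allocated group, and report completers only as supplementary. If the statistical analysis plan already says this, a sentence in the article is enough.
- **Missing data.** Replace the claim of robustness with a statement that the model is valid under missing at random given the modelled data.
- **Safety wording.** Reconcile Table 1 with Ethics and dissemination on which events end participation and in which part of the study.

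The cost is a few sentences of amendment and slightly more follow-up effort, using the online form or call already planned. The total of 100 need not change. The estimate may be somewhat smaller because less engaged patients stay in. The follow-up change has to be made before outcomes fall due.
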